#### Treatment retention

If the patient discontinues treatment, the therapist fills out a questionnaire about the reasons for dropout. In an exit interview, the patient is motivated by the research assistant to complete the future measurements. If the patient leaves treatment before the end of the protocol and both therapist and the patient regard the treatment as successful, the patient is considered an early completer.

### Participant timeline {13}

An overview of the timeline, interventions and assessments is presented in Table 1.

### Sample size {14}^3^

First, the required sample size was calculated to compare the three types of active treatments. Three pairwise comparisons will be conducted between the active treatment arms (PG vs. SFGT, PG vs. GST; SFGT vs. GST). To detect a medium effect size (*f* = 0.11) in a pairwise comparison of pre-post change between two active treatment arms, with *f*(*v*) = 0.2460 and Cohens *d* = 0.492, with Bonferroni-corrected alpha = 0.0167, a power of 0.80 and within-person correlation coefficient = 0.60, 88 patients are needed per arm. Because three types of therapies will be compared, 3 × 88 = 264 participants are needed to perform three pairwise comparisons. A medium effect size (*f* = 0.11^4^) is chosen to detect a clinically meaningful difference, as opposed to a smaller effect size. The correlation of 0.60 is an educated guess of the correlation between repeated assessments based on the previous RCTs the authors conducted.

The final analysis will be conducted with mixed regression on time series: the change in slope over time between two treatments. Because power analysis for mixed regression is complex and based on complex assumptions about the covariance-structure, a simplified approach was chosen by conducting a power analysis on the pre-post change.

In this study, we must take into account the correlation of observations within group psychotherapy, with an assumed Intra Class Correlation of 0.1. ([88], page 186). Therefore, we will increase the needed numbers with 10%, resulting in a total of 290 participants.

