### Objectives {7}

The aim of this pragmatic randomized clinical trial is to compare the effectiveness and cost-effectiveness of three group therapy formats that are regularly delivered in clinical practice to patients with a Cluster-C PD in a superiority study design. The primary outcome is the severity of the Cluster C-PD. The slopes over time of the three treatments (GST-C, SFGT and PG) from baseline to 24 months will be compared. Because of the variable durations of the treatments, we will make a comparison over a time window of 24 months, with assessments taking place at baseline, 3, 6 and 9 months, and at the different end points of the treatments at 12, 18 and 24 months, respectively. Next to the a priori tests over 24 months, we will explore differences between the outcomes of the three treatments on the slopes over time between start of treatment and the respective (different) end points. Differences in outcome at 36 months follow-up will be studied separately. No hypothesis was formulated about the direction of the difference.

The second aim is to study potential mechanisms of change both across therapies and for each specific theoretical framework by determining mediators in repeated measurements during and after therapy, across treatment conditions [58]. Group cohesion, group climate and working alliance are chosen as hypothesized general working mechanisms for group therapy. Another focus of research is the relationship between specific treatment interventions, mediators and outcome. The hypothesis is that certain interventions will be stronger connected to mediators and outcome than others. For example, we expect group dynamic interventions to be positively related to group cohesion.

The third aim is to study potential predictors and its moderating impact on outcome. The hypothesis is that for patients with higher levels of childhood trauma, schema therapy will be more effective, because of its use of trauma-oriented techniques, such as imaginary rescripting [34, 74]. Another hypothesis is that a more structured therapy such as GST-C will yield better results for patients with more severe personality pathology, e.g. borderline personality organization [54]. These patients are less able to tolerate high anxiety levels which can be provoked by the unstructured and exploratory character of PG [39]. Autism traits and vulnerable narcissism will be studied exploratively.

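### With exactly three arms, Bonferroni at 0.0167 is valid but gives up power that Shaffer's step-down recovers at the same sample size and the same 5% familywise error

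*Protocol article*

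**What the plan says.** The Sample size section {14} of the protocol article plans all pairs of the three treatments: "Three pairwise comparisons will be conducted between the active treatment arms". Each pair is sized "with Bonferroni-corrected alpha = 0.0167, a power of 0.80" at d = 0.492 on pre-post change. This gives 88 per arm and 264 in total, raised by 10% to 290 for correlation within therapy groups.

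The Objectives section {7} adds: "No hypothesis was formulated about the direction of the difference". All three comparisons are therefore two-sided and none has priority.

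The section on statistical methods for primary and secondary outcomes {20a} describes the mixed models but names no overall test, no ordering of the pairs and no other multiplicity procedure. The 0.0167 is the only error-control level in the article.

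**The concern.** Bonferroni guards against all three nulls being true at every step. With three arms that is more protection than needed after the first rejection. If arms A and B differ, a third arm C cannot equal both, so at most one of the two remaining nulls can be true, and each can be tested at the full 0.05 without raising the familywise error. Holding all three pairs at 0.0167 gives up this information.

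At stake is power on the three comparisons that form the trial's main question. The article has little to spare: the Limitations section concedes that dropout was not allowed for, and clustering is covered only by the 10% increase.

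**Working it through.** **Inputs (Sample size section).** f = 0.11, within-person correlation 0.60, alpha 0.0167, power 0.80, three pairs. Two-sided testing is inferred from the non-directional objective.

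**Reproducing the plan.**
- f(V) = 0.11 × √(2 / (1 − 0.60)) = 0.2460, and d = 2 × 0.2460 = 0.492. Both match.
- 0.05 / 3 = 0.0167.
- A two-sided two-sample t test at 0.0167 with d = 0.492 needs 88 per arm (noncentral t, power 0.8005). The normal approximation gives 87. A one-sided normal approximation gives 73, so the plan's figure is two-sided.
- 3 × 88 = 264, and 264 × 1.10 = 290.4, stated as 290.
- At an unadjusted 0.05, 88 per arm would give power 0.90. This is the ceiling for any multiplicity procedure here.

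**Procedures compared** (88 per arm, pooled variance with 3 × 88 − 3 = 261 degrees of freedom, independent patients, 1,000,000 simulated trials per scenario).
- Bonferroni: reject a pair if |t| > 2.410.
- Shaffer: if the largest |t| exceeds 2.410, reject every pair with |t| > 1.969.
- Overall test: if the 2-df F test is significant at 0.05, reject every pair with |t| > 1.969.

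| Scenario | Quantity | Bonferroni | Shaffer | Overall test first |
|---|---|---|---|---|
| Third arm equal to one of the pair | each true difference (0.492) | 0.803 | 0.867 | 0.881 |
| same | both true differences found | 0.692 | 0.819 | 0.832 |
| Third arm midway | extreme pair (0.492) | 0.803 | 0.816 | 0.829 |
| same | each half-size pair (0.246) | 0.220 | 0.355 | 0.362 |
| Arms spaced 0.492 apart | all three differences found | 0.615 | 0.804 | 0.804 |
| All arms equal | familywise error | 0.044 | 0.044 | 0.050 |
| Two arms equal, third 0.492 away | familywise error | 0.017 | 0.049 | 0.050 |
| Two arms equal, third far away | familywise error | 0.017 | 0.050 | 0.050 |

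**Dominance.** Shaffer's first step is Bonferroni's own threshold and its later threshold is lower, so it cannot lose a Bonferroni rejection. The overall-test version can: with a 0.492 pair and the third arm equal or midway, it blocked a pair that Bonferroni rejected in 0.1% to 0.4% of trials.

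**Size of the interval mismatch under Shaffer.** A pair rejected by Shaffer but not by Bonferroni has a Bonferroni interval that includes zero. The expected number of such pairs per trial is the sum over pairs of the difference in rejection rates.
- Third arm equal to one of the pair: (0.0494 − 0.0166) + (0.8669 − 0.8032) + (0.8668 − 0.8032) = 0.16.
- Third arm midway: (0.3551 − 0.2204) + (0.8156 − 0.8026) + (0.3553 − 0.2204) = 0.28.

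**The case against.** **Nothing is wrong as written.** Bonferroni is valid and the arithmetic is correct, so preferring another valid procedure may look like taste. The first part stands in full. The second does not quite: Shaffer rejects whatever Bonferroni rejects, at the same familywise level, so on decisions alone there is no trade-off to weigh.

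**The 0.0167 is a planning input.** It appears only in the sample size calculation, which the article itself describes as simplified, and the final testing rule may sit in an analysis plan that is not shown. It is fair to say that reading 0.0167 as the decision rule is an inference. But the article ties that level to the three planned comparisons and gives no other rule, so improving it answers a stated choice and does not complain of a gap.

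**The gain may be small.** The article places SFGT midway between the other two treatments in structure and duration. If effects followed that order, the extreme pair would gain under two points with Shaffer, and the half-size pairs would stay badly underpowered at 0.355. This stands, although the article predicts no order of effects.

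**Intervals.** Bonferroni has simple simultaneous intervals and a stepwise test does not. This is a real cost, although the article promises no such intervals.

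**Stronger readings to resist.** A reader might infer that the multiplicity control or the sample size is mistaken, that the change is free, or that it would make good any shortfall from clustering and dropout. The documents support none of these. The figures reproduce, the loss of matching intervals is a cost, and both clustering and dropout would lower every power figure in the table.

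**Conclusion.** The point holds as an inexpensive improvement. With three arms, all three pairs compared and no priority among them, Shaffer's step-down keeps the 5% familywise error and raises power at 88 per arm. Power for a true difference of 0.492 goes from 0.80 to 0.87 if the third arm equals one of the pair, but only from 0.80 to 0.82 for the extreme pair if the third arm is midway. The midway half-size pairs gain most, from 0.220 to 0.355, and remain weakly powered.

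These figures rest on the article's simplified pre-post basis with independent patients and complete data. The logical step from three arms carries over to the pairwise contrasts of the mixed model, but the power values would be lower there once clustering and dropout are counted. The argument is specific to three arms.

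**What to change.** State, before outcome data are analysed by arm, that the three pairwise contrasts on the primary outcome are tested by Shaffer's step-down: the smallest p-value against 0.0167 and, if that is met, the other two against 0.05, all two-sided. Leave the sample size and the Bonferroni planning value unchanged, and treat the gain as reserve for clustering and dropout.

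An overall 2-df treatment test at 0.05 followed by each pair at 0.05 is an acceptable alternative with slightly more power, provided its rare blocking of a Bonferroni rejection is accepted.

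The change costs one sentence and no patients. If Bonferroni intervals are reported alongside, the text should say in advance that the stepwise test governs the decision and that an interval may include zero for a pair declared different.

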### Interventions

#### Intervention description {11a}

GST-C is based on the protocol of Farrell and Shaw [30] that has been adapted for the Cluster-C patient [86]. The protocol consists of 30 weekly sessions of 90 min, combined with facultative individual sessions with a maximum of 300 min in total, followed by 4 monthly group booster sessions of 60 min each. Change of schema modes with experiential techniques constitutes the core of the GST-C. The structure of the group is semi-open, with new participants enrolling every 10 sessions, with a maximum of 9 participants in total. The group is led by two therapists, with a third therapist appointed to step in if one of the two therapist is absent. Therapists both have an additional minimum registration of junior schema therapist and are trained in group schema therapy according to Farrell and Shaw [30].

SFGT combines a structured schema-focused approach with an open, unstructured part in one session, thereby giving more room to group dynamics than traditional schema therapy groups [1]. This format is developed to be especially suited for patients with a Cluster-C PD, enabling a focus on intrapersonal and interpersonal dynamics. SFGT consists of three phases, with every 20 sessions new participants enrolling in the group and others terminating. Participants commit to a minimum of 40 sessions, with a maximum of 60. Every session starts with 60 min structured schema therapy interventions, mainly experiential exercises aimed at schema mode change. This is followed by an open group dialogue of 45 min in which group dynamic interventions play a central role using, if appropriate, schema language to interpret and communicate. The group is led by a head therapist and a co-therapist. The head therapist has a minimum registration of junior schema therapist.

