PG makes use of psychodynamic theories and interventions in combination with a focus on the group dynamics [10]. The sessions have an open dialogue character that facilitates a group process in which personality patterns emerge. This enables the therapist to intervene on both the individual level of the patient and on the interaction between patients and the group as a whole. Typical for the psychodynamic framework is to facilitate insight by relating emotions in the here and now to earlier experiences during life [39] and to interpret the transference with the group therapists and the relation with group members as repetitions of earlier relational experiences [10, 62]. In addition, frequently occurring defence and resistance phenomena are discussed to improve the group process, thus making underlying or avoided feelings or fantasies more conscious and beneficial for the patients [10]. PG gives room to spontaneous interactions between group members, facilitating the possibility of interpersonal learning. Through feedback of the group members and group leaders and self-observation, the increase in insight and self-understanding, change in self-image, activation of affects and change of defence style is facilitated. The duration is 80 sessions (2 years) with 90 min sessions. A new participant enrols when another terminates, with a maximum of 9 participants. The group is led by two group therapists, a head therapist and a co-therapist. The minimum qualification for the head therapist is an official specialisation in group therapy. All therapists are trained in a PG protocol that describes the theoretical framework, process and interventions [90], to increase allegiance of therapists and testing adherence.

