Another limitation is the different duration of the treatment modalities. Although we ruled out the confounding effect of time by setting the end point of the main outcome measurements at 24 months, it will not be clear what the confounding effect of dosage could be. Difference in dosage is due to the pragmatic character of the study in researching existing group therapy formats, with varying duration and dosage. Because of these different dosages, determining cost-effectiveness at follow-up is of extra importance in this study. However, the difference in dosage and amount of structure in the compared therapies gives, in combination with the extensive study of predictors and potential moderators, the opportunity to gain valuable knowledge about which therapy is best for which type of Cluster C patient, hereby optimizing the possibility of matched or personalized care.

To conclude, in the sample size calculation, we did not adjust for dropout, which could negatively affect the power. Nevertheless, mixed regression with multiple measurements over 2 years is expected to balance out this potential loss of power because of the particular strength of this type of analysis.

As far as we know, G-FORCE will be the first large pragmatic RCT on the effectiveness of group therapy for Cluster-C PDs, contributing to growing evidence on effective Cluster-C treatments and group psychotherapy. With its focus on possible predictors and mediators, G-FORCE will increase our understanding on which therapy works for whom and why, helping to recommend the best available clinical treatment for the individual patient with a Cluster-C PD diagnosis.

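### The clustering allowance uses the ICC of 0.1 as a 10% increase; with 5 to 9 trial patients per therapy group, 290 patients give about 55–68% power on the protocol's own calculation, not 80%

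*Protocol article*

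**What the plan says.** The Sample size section of the Protocol article bases the trial on three pairwise comparisons of pre-post change, with d = 0.492, within-person correlation 0.60 and "Bonferroni-corrected alpha = 0.0167, a power of 0.80". This gives 88 patients per arm, 264 in all. For correlation within therapy groups it proceeds "with an assumed Intra Class Correlation of 0.1" and concludes: "Therefore, we will increase the needed numbers with 10%, resulting in a total of 290 participants". No group size enters that step.

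Group sizes appear under Intervention description. GST-C groups are semi-open, "with a maximum of 9 participants in total". For PG: "A new participant enrols when another terminates, with a maximum of 9 participants". SFGT also has rolling entry, every 20 sessions, but no group size is given.

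The Sample size section says that the final analysis will be mixed regression and that the pre-post calculation is a simplification. The Limitations section adds that "in the sample size calculation, we did not adjust for dropout, which could negatively affect the power", and expects mixed regression over the repeated measurements to make up for this. It gives no calculation.

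**The concern.** An ICC is not an inflation percentage. The variance of an arm mean rises by 1 + (m − 1) × ICC, so the cost of clustering depends on how many trial patients share a group. Leaving m out amounts to assuming two trial patients per group. That would mean about 145 groups (290 / 2) at one centre with four locations, which does not fit groups of up to 9.

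What is at stake is the stated power. This is a superiority comparison of three active therapies without a control arm, so a pairwise result that is not significant is quite possible. How much such a result says about medium-sized differences depends on the power that the trial really had.

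**Working it through.** **Inputs from the protocol.** d = 0.492 (f = 0.11, f(V) = 0.2460), alpha = 0.0167, power 0.80, within-person correlation 0.60, 88 per arm, ICC 0.1, total 290 allocated 1:1:1 (Sample size; Trial design). The test is taken as two-sided because Objectives states no direction.

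**Reproducing the protocol's figures.**
- f(V) = 0.11 × √(2 / (1 − 0.60)) = 0.2460, and d = 2 × 0.2460 = 0.492.
- A two-sided t-test with 88 per arm, d = 0.492 and alpha 0.0167 has power 0.800 (noncentral t).
- 264 × 1.10 = 290.4, stated as 290.

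The unclustered calculation is therefore correct, and the 10% step is confirmed as a plain multiplication by 1.10.

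**What 1.10 implies.** Setting 1 + (m − 1) × 0.1 = 1.10 gives m = 2. With groups of 9, a factor of 1.10 would need an ICC of 0.10 / 8 = 0.0125, one eighth of the stated value.

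**Power with the design effect.** DE = 1 + (m − 1) × 0.1; effective n per arm = (290 / 3) / DE = 96.67 / DE; power from the noncentral t at d = 0.492 and alpha 0.0167. The lower sizes are assumptions; 9 is the stated maximum for GST-C and PG.

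| m | DE | effective n per arm | power | d detectable with 80% power | total for 80% power at d = 0.492 (264 × DE) |
|---|---|---|---|---|---|
| 2 | 1.1 | 87.9 | 0.80 | 0.49 | 290 |
| 3 | 1.2 | 80.6 | 0.76 | 0.51 | 317 |
| 5 | 1.4 | 69.0 | 0.68 | 0.56 | 370 |
| 7 | 1.6 | 60.4 | 0.61 | 0.60 | 422 |
| 9 | 1.8 | 53.7 | 0.55 | 0.63 | 475 |

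**Can the repeated visits restore the power?** Take the seven times listed in Objectives (0, 3, 6, 9, 12, 18, 24 months), outcome variance 1, exchangeable correlation 0.6 and exactly linear change.
- The pre-post change has variance 2 × (1 − 0.6) = 0.8. An ICC of 0.1 on change puts 0.08 of it between groups.
- The difference to detect is 0.492 × √0.8 = 0.440.
- In units of 24 months, the visit times have a sum of squares about their mean of 0.7455.
- The residual variance is 0.36 if the group component is counted inside the 0.8, or 0.40 if it is added to it.
- The variance of an arm's mean change is (m × 0.08 + residual / 0.7455) / 96.67.

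At m = 9 with residual 0.36, the numerator is 0.72 + 0.483 = 1.203. The standardised difference is 0.440 / √1.203 = 0.401 and power is 0.65. With residual 0.40, power is 0.62. The same steps give 0.69–0.72 at m = 7 and 0.77–0.80 at m = 5. All of these are before dropout.

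**The case against.** Nobody can defend the 10% step as a formula. The fair objections concern its size.

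- **Nine is a ceiling.** It is stated for GST-C and PG only, and SFGT enters two of the three comparisons. These are routine-care groups, and nothing says that every seat is held by a trial patient. This stands. A reader might infer that the trial's power simply is 55%, but the documents support that only as the value at the stated maximum, on the pre-post simplification.
- **The planned analysis uses all visits.** This stands in part. A reader might infer that repeated visits cannot help because they leave between-group variance untouched. The calculation shows that they do help, by 7 to 10 points at m = 9 and almost back to 0.80 at m = 5. The model behind that gain is favourable, however: no random slopes, and straight-line change although the therapies end at 12, 18 and 24 months.
- **Rolling entry could make clusters larger than 9.** A reader might infer much lower power. The documents do not say how many trial patients pass through one group, and patients who never attended together need not share the full ICC, so no figure is put on this.
- **Dropout is already disclosed as a limitation.** True. No dropout rate is given, so a loss from it cannot be calculated from the documents. What remains is an expectation of balance with nothing behind it.
- **A group random effect is planned, if estimation allows.** The issue is therefore mainly planning power rather than a biased analysis. That also stands, although an analysis that drops the effect would understate the standard errors.

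The source cited for the ICC was not available, so the value of 0.1 is taken as given.

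**Conclusion.** The point holds. The 10% increase does not follow from an ICC of 0.1, and the stated power of 0.80 is not what 290 patients deliver under the protocol's own inputs. With 5 to 9 trial patients per group, power per pairwise comparison is about 0.68 down to 0.55, which corresponds to 80% power for d of about 0.56 to 0.63. Repeated visits may raise this to 0.77–0.80 at m = 5 and 0.62–0.65 at m = 9, so they do not restore 80% at m = 7 to 9.

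The result rests on the protocol's ICC, applied to change; on a number of trial patients per group that the protocol does not state, here taken as 5 to 9 and equal across arms; and on no dropout. The direction does not depend on the exact m: even three per group gives 0.76 on the pre-post calculation.

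**What to change.** In Sample size, replace the 10% rule by 1 + (m − 1) × ICC, state the assumed number of trial patients per group for each therapy (including SFGT), and restate what 290 patients deliver. Possible wording:

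> *With an ICC of 0.1 and 5–9 trial patients per therapy group, 290 patients give about 55–68% power for d = 0.492, or 80% power for d of about 0.56–0.63, on the pre-post calculation and before dropout.*

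If credit is to be taken for the mixed model, report that calculation with its assumptions on visits, correlation and group variance.

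In Limitations, support the expectation that mixed regression balances out the dropout loss with a calculation that includes clustering, or remove it.

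The cost is rewording two sections and accepting a less favourable stated power. No extra patients are needed, and treatment and data collection do not change.
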